### Participant timeline {13}

The study is presented to children and their parents during a selection visit, along with appropriate information letters. If the children/parents show interest in the study, the 1st evaluation visit for the parents and children is organized and their group assignment occurs. Therapy begins after randomization and lasts about 5 months. Then evaluation visits at 5 months (after therapy) and 8 months (post-therapy evolution) are planned. The timeline of the therapy is summarized in Figs. 1 and 2.

**Fig. 1 Fig1:**
[figure not shown]
Study design

**Fig. 2 Fig2:**
[figure not shown]
Participant timeline

### Sample size {14}

We could not find prior studies on psychological interventions for ADHD using a similar sample, assessments, and research outcomes. Thus, to estimate the sample size, we used the following: (i) preliminary data collected from a pilot study on the experimental intervention (*n* = 30, personal data) and (ii) previous data on the efficacy of the Barkley program on a large sample (van den Hoofdakker et al., 2007). We compared the change in the number of patients fulfilling the diagnostic criteria for ADHD in both samples from baseline to the end of the therapy, although the assessment instruments were different (ADHD Rating Scale in our sample versus the Conners Parents Rating Scale).

To highlight a difference of relative reduction of risk of 9% (*SD* = 20.6%) between the two groups: 15% parental guidance (van den Hoofdakker et al. 2007) versus 24% mCBT ([name], personal data), with a two-sided alpha risk of 5% and a power of 90%, it is necessary to recruit 111 children per group. To take account of a potential 10% loss during follow-up, 124 children per group will be recruited, i.e., 248 children. The statistical unit corresponds to a family, which includes a calculated sample size of children with ADHD plus one or both parents.

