#### Control group (Barkley program)

The Barkley program is specifically conceived for parents of children with ADHD, either individually or in groups of 6 to 8 families, with twelve 90-min sessions, occurring twice a month. The objective of this program is to train parents to cope with the difficult situations they encounter, to learn effective control strategies that are coherent and adapted to the “deviant” behavior of their children in order to reduce the intensity of events and their consequences on family life. All this inevitably involves the improvement of family relationships through an essential improvement of the image that parents have of themselves, the image the child has of him/herself, and overall family functioning.

Each session focuses on a “theme” or a particular situation: practical exercises are offered to families to improve communication, adjust the educational responses, analyze the behavior of the child, and anticipate crises in order to avoid them. These practical exercises are practiced at home. A typical session has the following structure: a 30-min review of exercises practiced at home, 60 min: theme of the day’s and new exercises.

The control group facilitator cannot participate in mCBT therapy to avoid bias. The Barkley program is already in use by all participating centers and training per se is not required. Nevertheless, a standardized consensus has been established between the centers to reduce variability before beginning the study and regular meetings are made annually to ensure that the program is followed faithfully.

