## Assignment of interventions: allocation

### Sequence generation {16a}

Families are randomized to either study arm in a 1:1 ratio. Randomization lists consisting of centralized randomly sized blocks are established per center. These lists are the responsibility of an independent methodologist at the BESPIM. A specifically designed SAS program (Cary, NC, USA) is used to carry out randomization.

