## Statistical methods

### Statistical methods for primary and secondary outcomes {20a}

The primary outcome is the change from baseline in the ADHDRS-PI at 5 months. If required for meeting normality, the ADHDRS-PI scores will be appropriately transformed (e.g., Box-Cox transformation). A Student’s test will be used to compare the two groups. If the conditions for use of a Student’s test are not met, a non-parametric Mann-Whitney test will be used. This analysis will be completed by a modeling analysis to take into account clustering effects. Indeed, in our study, randomization to treatment is done on an individual basis; however, the experimental and control treatments are administered to a group so that several individuals receive the intervention together by the same therapists; the observations within the group therapy will likely be correlated within groups (clustering effect). We will use multilevel mixed-effects models to assess the treatment effect on the primary outcome: the ADHDRS-PI score at 5 months by adjusting for cluster effects and ADHDRS-PI score at baseline.

There is no a priori reason for carrying out per-protocol analyses in the present study. All analyses will therefore be performed on the intention-to-treat population. The level of significance is set at *p* < 0.05 (bilateral). The statistical analysis will be performed by the BESPIM using SAS software (SAS Institute, Cary, NC, USA) version 9.4 (or higher) or the R statistics environment (R Development Core Team 2008) version 3.3.1 (or higher).

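### The 90% power in the sample size section assumes independent children and makes no allowance for the therapy-group correlation that the analysis section expects, so it is unsupported as stated

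*Protocol article*

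**What the plan says.** Sample size {14} sets out to detect "a difference of relative reduction of risk of 9" percentage points (15% with parental guidance against 24% with mCBT, SD 20.6%). It states that "with a two-sided alpha risk of 5% and a power of 90%, it is necessary to recruit 111 children per group". Allowing for 10% loss gives 124 per group, 248 in all. The section names the family as the statistical unit and mentions no therapy-group size, ICC or design effect.

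Statistical methods {20a} says that "the experimental and control treatments are administered to a group so that several individuals receive the intervention together by the same therapists", and that this will probably make outcomes within a therapy group correlated. It names a Student's test first, then a multilevel mixed-effects model adjusting for clustering and for the baseline ADHDRS-PI score. Methods for additional analyses {20b} adds that the ICCs estimated here are needed to size later trials.

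On group size, the Control group section says that Barkley sessions are given "either individually or in groups of 6 to 8 families". No size is given for the mCBT groups. Sequence generation {16a} confirms that "Families are randomized to either study arm in a 1:1 ratio".

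**The concern.** The two sections rest on different assumptions. The sample size treats each child's outcome as independent of every other's, while the analysis section says the outcomes are likely to be correlated within therapy groups. {20b} also accepts that the ICC determines sample size. Positive correlation within groups reduces the information carried by 111 children, and 111 leaves nothing spare to absorb that.

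The stated power affects how a null result is read. If the trial is described as having 90% power for a 9-point difference when the real figure is lower, a null result will be taken as stronger evidence against that difference than it is.

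**Working it through.** **Reproducing the plan's figure.** Inputs from {14}: difference 9, SD 20.6, two-sided 5%, power 90%; 1:1 allocation from {16a}.

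- Standardised difference: 9/20.6 = 0.437.
- Normal approximation: n = 2 × (1.960 + 1.282)² × 20.6²/9² = 110.1, i.e. 111 per group.
- t-based: n = 111.07, and power at 111 is 89.98%.
- Loss to follow-up: 111/0.9 = 123.3, i.e. 124 per group.

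Both stated numbers reproduce with no term for clustering. The arithmetic is right for independent observations.

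**Adding clustering, no baseline adjustment.** Assumptions: 111 evaluable per arm; m = 6, 7 or 8 families per group in both arms (stated only for Barkley, assumed for mCBT); ICC 0.01 to 0.10 (not in the documents). Design effect DE = 1 + (m − 1) × ICC; effective n = 111/DE; t-based power for 9 with SD 20.6.

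| ICC | DE (m = 6, 7, 8) | Effective n | Power (%) | Difference detectable with 90% power, m = 7 (percentage points) |
|---|---|---|---|---|
| 0 | 1 | 111 | 90.0 | 9.0 |
| 0.01 | 1.05, 1.06, 1.07 | 105.7, 104.7, 103.7 | 88.5, 88.2, 87.9 | 9.3 |
| 0.02 | 1.10, 1.12, 1.14 | 100.9, 99.1, 97.4 | 87.0, 86.4, 85.8 | 9.5 |
| 0.05 | 1.25, 1.30, 1.35 | 88.8, 85.4, 82.2 | 82.5, 81.0, 79.5 | 10.3 |
| 0.10 | 1.50, 1.60, 1.70 | 74.0, 69.4, 65.3 | 75.2, 72.4, 69.8 | 11.4 |

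If only one arm were clustered, the variance factor is the mean of 1 and DE. For m = 6 and 8 that is 1.125 and 1.175 at ICC 0.05 (power about 86% and 85%), and 1.25 and 1.35 at ICC 0.10 (about 83% and 80%).

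**Adding the planned baseline adjustment.** With equal variances σ² at baseline and 5 months and correlation ρ, the change score has variance 2σ²(1 − ρ) and the baseline-adjusted residual has σ²(1 − ρ²). The ratio is (1 + ρ)/2, which is 0.75 at ρ = 0.5 and 0.85 at ρ = 0.7. How much of the between-group part the adjustment removes is unknown, so two cases are shown for m = 7:

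- both parts shrink: variance factor = (1 + ρ)/2 × DE;
- only the within-group part shrinks: variance factor = (1 + ρ)/2 × (1 − ICC) + 7 × ICC.

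| ICC | Factors, ρ = 0.5 | Power (%) | Factors, ρ = 0.7 | Power (%) |
|---|---|---|---|---|
| 0.02 | 0.840, 0.875 | 94, 93 | 0.952, 0.973 | 91, 91 |
| 0.05 | 0.975, 1.063 | 91, 88 | 1.105, 1.158 | 87, 85 |
| 0.10 | 1.200, 1.375 | 84, 79 | 1.360, 1.465 | 79, 76 |

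**The Student's test.** Ignoring clustering, its true two-sided error is 2 × [1 − Φ(1.96/√DE)]. Over m = 6 to 8 this is about 5.6-5.8% at ICC 0.01, 8.0-9.2% at 0.05 and 11-13% at 0.10. Under the expected clustering it does not hold its 5% level, so it cannot support the stated figure.

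**The case against.** The strongest reply is that the table without baseline adjustment does not describe the model the protocol plans. The only cluster-aware analysis in {20a} also adjusts for baseline. At ρ = 0.5 that takes power above 90% at ICC 0.02 and roughly to 90% at 0.05. This stands. A reader might infer from the missing design effect that the trial is underpowered, that 90% cannot be reached, or that more families must be recruited. The documents do not support any of these, because the quantities that decide the matter (ICC, mCBT group size, baseline correlation) are not in them.

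It also stands that Barkley may be delivered individually, although {20a} describes both treatments as given to groups; that at ICC 0.01 the loss is only one to two points; and that the eventual estimate and confidence interval from the multilevel model will take account of clustering whatever {14} says.

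Two limits apply to the reply. {14} neither claims nor quantifies a gain from baseline adjustment, so that gain cannot be what supports its 90%. And the (1 + ρ)/2 factor applies to an absolute change score with equal variances, whereas {14} describes its 9% and 20.6% as a relative reduction. The credit holds only if 20.6% can be treated as the SD of an absolute change score.

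**Conclusion.** The concern holds as a mismatch between the stated power and the protocol's own expectation of clustering. It is not an arithmetic error and not proof of a shortfall. For the comparison without baseline adjustment, 90% holds only if the ICC is zero. With 6 to 8 families per group in both arms and ICC 0.01 to 0.10, power for that comparison runs from about 89% down to 70%. For the planned baseline-adjusted model with 7 per group, ICC 0.02 to 0.10 and ρ = 0.5, it runs from about 94% down to 79%; recovery is smaller at higher ρ. A material shortfall under the planned model therefore needs an ICC towards the upper end of the range or a high baseline correlation. The missing allowance is certain; the size of its effect is not. It should be fixed, but it does not threaten the trial's validity.

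**What to change.** Keep 248. In {14}, replace the single 90% with power for the multilevel baseline-adjusted analysis, or with the difference detectable with 90% power in percentage points. Give it over stated ranges of ICC (0.01 to 0.10), therapy-group size in each arm and baseline to 5-month correlation. State the mCBT group size, whether Barkley is delivered in groups in this trial, and whether 20.6% is the SD of an absolute or a relative change. Add that 90% applies to the unadjusted comparison only if the ICC is zero.

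The cost is a rewording and a stated power that may be less favourable. No extra families are needed, and the endpoint, analysis and conduct do not change.

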### Recruitment {15}

Approximately 650 families per year consult at Nimes University Hospital requesting help in dealing with an ADHD child. As this is the smallest establishment participating in this protocol, we expect larger potential recruitment pools for the other centers. Our target rhythm for inclusions is 1–2 families per month and per center (on average).

This is largely inferior to potential recruitment pools in order to take into account the time constraints associated with randomized group therapy, the need to implement the interventions during the school year, and the possibility that certain families may choose not to participate and also to have a feasible inclusion curve.

## Assignment of interventions: allocation

### Sequence generation {16a}

Families are randomized to either study arm in a 1:1 ratio. Randomization lists consisting of centralized randomly sized blocks are established per center. These lists are the responsibility of an independent methodologist at the BESPIM. A specifically designed SAS program (Cary, NC, USA) is used to carry out randomization.

### Concealment mechanism {16b}

Patient inclusions are performed via an online software called “Inclusio” (inclusio.bespim.fr), an inclusion-randomization software designed for clinical research projects. Following user login, patient identification (first letter of last name + first letter of first name + year of birth) and verification of screening and exclusion criteria, the treatment number for blind studies, or the study arm for open-label studies are indicated to the user. It is impossible to modify the order of randomization; patient assignment to a study arm and a randomization number is definitive. The program provides real-time inclusion alerts to study staff requesting such alerts.

### Implementation {16c}

The allocation sequence is generated by an independent methodologist at the BESPIM. Patient enrolment is carried out by including psychiatrists. Randomization is carried out after patient inclusion and after baseline assessments by participating psychologists (i.e., not the including psychiatrists, who are also the outcome assessors). The e-santé team at the BESPIM is in charge of setting up Inclusio for the needs of the project (note: statistical analyses are carried out at the family level and safety reporting is carried out at the individual level).

## Assignment of interventions: blinding

### Who will be blinded {17a}

Baseline assessments are made before randomization, so these are blinded.

Due to the nature of the intervention, neither participants nor staff can be blinded to allocation, but are strongly inculcated not to disclose the allocation status of the participant at the follow-up assessments. Patients cannot be blinded, but are asked to not reveal their group status to anybody outside their group, not even their treating psychiatrist. Furthermore, the hypotheses tested are not communicated to patients (i.e., the patients are not informed on the supposed superiority of one group over another). Therapy care providers (psychologists) cannot be blinded. In order to make assessments as objective as possible, outcome assessors (psychiatrists) are different from the therapy providers (psychologists), and every attempt is made to keep outcome assessors blinded to patient group status. To control for the success of blinding, a “guess-the-group” question is addressed to outcome assessors. Outcome assessor responses are compared to expected results due to chance (see the Statistical methods section).

Data analysts will not be involved in trial field logistics and will be blinded. During analyses, when group assignments are first required they will only be revealed as “group A” or “group B”. Only when analyses have been completed will the exact nature of groups be revealed.

### Procedure for unblinding if needed {17b}

Not applicable, the design is open label with only outcome assessors being blinded so unblinding will not occur.

## Data collection and management

### Plans for assessment and collection of outcomes {18a}

Clinical observations are recorded in the case report form as the study progresses.

The instruments/questionnaires to be administered:

1. Schedule for Affective Disorders and Schizophrenia for School-Age Children–Present and Lifetime Version (K-SADS-PL)

2. The Clinical Global Impression Scale (CGI-S)

3. The Children’s Global Assessment Scale (CGAS)

4. ADHDRS-PI

5. Children’s Depression Inventory (Kovacs 1981)

6. Adult ADHD Self-Report Scale (ASRS)

7. the Parental Authority Questionnaire (PAQ)

8. Parental–Developmental Disorders–Quality of Life (PAR-DD-Qol)

9. Hospital Anxiety and Depression Scale (HADS)

10. The Conners questionnaire for parents

11. Multidimensional Anxiety Scale for Children (MASC)

12. Rosenberg Self-Esteem Scale

13. The Conners questionnaire for teachers

Please refer to the “Outcomes {12}” section for a description of the instruments and references.

### Plans to promote participant retention and complete follow-up {18b}

The study clinical research technician maintains contact with families and teachers. Study calendars are distributed to families as early as possible in the study and kept up-to-date by the study clinical research technician. Reminders are sent to families in the week preceding each evaluation.

### Data management {19}

Performed in line with the international conference on harmonization of technical requirements for registration of pharmaceuticals for human use (ICH). The related documents are stored on the Department of Biostatistics, Epidemiology, Public Health and Medical Information at the Nimes University Hospital (BESPIM). Electronic case report form (eCRF) fields are formatted so as to enforce homogenous value types and require confirmation especially for out-of-expected-range values. All modifications are fully traceable (who, when, why?) to allow a complete audit trail. An electronic signature by the investigator engages his/her responsibility. The software used to create eCRFs is hosted on a website within Nimes University Hospital. Access to this software is secured via a password. The data collected through generated eCRFs are subject to daily backup on a secure network. The network is connected to the Internet; access is protected by a firewall. Clinical study data is stored in a specific directory on the server. Only network administrators and BESPIM authorized professionals have access to this directory.

Data management and statistical analysis are provided by the BESPIM. The conditions of transfer of all or part of the research database are decided by the research sponsor and are subject to a written contract.

The following measures are taken to implement confidentiality:
The required information technology is located at the BESPIM; access is controlled and secured.Data are stored on a server hosted in a secure room at Nimes University Hospital.

In case of hardware or software problems, a specific safety procedure has been implemented.

The export of data for analysis is conducted by a BESPIM authorized professional.

The closing of the trial including the closure of the centers is conducted in accordance with Good Clinical Practice and ICH. Medical and administrative records and CRFs are kept for the duration of the study in the service and then archived for a minimum of 30 years.

### Confidentiality {27}

In accordance with article R.5120 of the French Public Health Code, the investigators, as well as any persons collaborating in the study, will respect medical confidentiality especially as concerns the nature of the study, the persons participating in the study, and the obtained results.

The study protocol, documentation, data, and all other information generated are held in strict confidence. No information concerning the study or the data will be released to any unauthorized third party without prior written approval of the sponsor.

The investigator will ensure that the anonymity of each person involved in the study is respected. On all study-related documents, the patient is identified using only a unique, 7-character identification number, and the first letter of his/her last name, the first letter of his/her first name, and his/her year of birth. A patient identification list is maintained by the investigator (and only the investigator).

### Plans for collection, laboratory evaluation, and storage of biological specimens for genetic or molecular analysis in this trial/future use {33}

Not applicable. There will be no biologic specimens collected for storage.

## Statistical methods

### Statistical methods for primary and secondary outcomes {20a}

The primary outcome is the change from baseline in the ADHDRS-PI at 5 months. If required for meeting normality, the ADHDRS-PI scores will be appropriately transformed (e.g., Box-Cox transformation). A Student’s test will be used to compare the two groups. If the conditions for use of a Student’s test are not met, a non-parametric Mann-Whitney test will be used. This analysis will be completed by a modeling analysis to take into account clustering effects. Indeed, in our study, randomization to treatment is done on an individual basis; however, the experimental and control treatments are administered to a group so that several individuals receive the intervention together by the same therapists; the observations within the group therapy will likely be correlated within groups (clustering effect). We will use multilevel mixed-effects models to assess the treatment effect on the primary outcome: the ADHDRS-PI score at 5 months by adjusting for cluster effects and ADHDRS-PI score at baseline.

There is no a priori reason for carrying out per-protocol analyses in the present study. All analyses will therefore be performed on the intention-to-treat population. The level of significance is set at *p* < 0.05 (bilateral). The statistical analysis will be performed by the BESPIM using SAS software (SAS Institute, Cary, NC, USA) version 9.4 (or higher) or the R statistics environment (R Development Core Team 2008) version 3.3.1 (or higher).

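### The leading primary test is an unadjusted change-score test with a data-triggered change of scale or test; the adjusted model already planned should be the single primary analysis

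*Protocol article*

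**What the plan says.** Everything on this point stands in the protocol article, Statistical methods for primary and secondary outcomes {20a}, in this order:

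- Outcome: "The primary outcome is the change from baseline in the ADHDRS-PI at 5 months".
- Scale: "If required for meeting normality, the ADHDRS-PI scores will be appropriately transformed (e.g., Box-Cox transformation").
- Test: "A Student’s test will be used to compare the two groups". No covariate is named.
- Fallback: "If the conditions for use of a Student’s test are not met, a non-parametric Mann-Whitney test will be used".
- Model: "This analysis will be completed by a modeling analysis to take into account clustering effects". It is a multilevel mixed-effects model for "the ADHDRS-PI score at 5 months by adjusting for cluster effects and ADHDRS-PI score at baseline".

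The section also explains that children treated together by the same therapists will probably have correlated outcomes, and it gives this as the reason for the model. It does not rank the test and the model.

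Sample size {14} plans for "To highlight a difference of relative reduction of risk of 9% (*SD* = 20.6%) between the two groups" and concludes that "with a two-sided alpha risk of 5% and a power of 90%, it is necessary to recruit 111 children per group".

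**The concern.** Three things follow from the order in which {20a} sets out the analysis.

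1. **Precedence.** The simple test comes first and the model complements it. If the two disagree on significance, the section does not say which one decides superiority.
2. **What is reported.** Depending on how the data look, the headline result could be a difference in ADHDRS-PI points, a difference on a transformed scale, or a rank comparison with no mean difference attached. These summaries answer different questions, and only the first is in the units of the instrument.
3. **Efficiency and clustering.** The leading test uses the baseline score only by subtraction, which is never more precise than adjusting for it and is often less so. It also treats children from one therapy group as independent, although the section expects them not to be.

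At stake are a clear primary result and precision that the baseline measurement already makes available.

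**Working it through.** **Step 1. The plan's own figure.** Inputs from Sample size {14}: difference 9, SD 20.6, two-sided alpha 5%, power 90%.

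n per arm = 2 × [20.6 × (1.960 + 1.282) / 9]² = 110.1, rounded up to 111. With 10% loss, 111 / 0.90 = 123.3, rounded up to 124, so 248 in total. The stated figures reproduce exactly as an unadjusted comparison of two means. Power at 111 per arm is 90.2%. The sample size therefore matches the leading test.

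**Step 2. Precision of change score against baseline adjustment.** Let s be the SD at 5 months, k the ratio of baseline SD to 5-month SD, and rho the correlation between the visits. The documents give neither k nor rho, so both are assumptions.

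- Variance of the change: s² × (1 + k² − 2·rho·k)
- Residual variance after baseline adjustment: s² × (1 − rho²)
- Ratio, adjusted to change: (1 − rho²) / (1 + k² − 2·rho·k)

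The first variance minus the second is s² × (k − rho)², which cannot be negative. Adjustment therefore does not lose precision (apart from one degree of freedom), and it gains none only when k = rho. With k = 1 the ratio reduces to (1 + rho)/2.

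| rho (assumed) | ratio, k = 1 | ratio, k = 0.7 |
|---|---|---|
| 0.3 | 0.65 | 0.91 / 1.07 = 0.85 |
| 0.5 | 0.75 | 0.75 / 0.79 = 0.95 |
| 0.7 | 0.85 | 0.51 / 0.51 = 1.00 |

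The column k = 0.7 matters because entry requires an ADHDRS-PI above 27 (Eligibility criteria {10}). That cut restricts the baseline range but not the 5-month range, so equal SDs are doubtful. For equal precision the change-score test needs 1/ratio times as many families. That is 18% to 54% more if k = 1, and 0% to 18% more if k = 0.7.

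**Step 3. Illustration at the planned size.** This takes 20.6 as the SD of the change, which is a further assumption because {14} attaches it to a percentage reduction and not to ADHDRS-PI points. Clustering is ignored. With k = 1, adjustment at 111 per arm gives power of 98.1%, 96.4% and 94.2% for rho 0.3, 0.5 and 0.7. For 90% power, 72, 83 and 94 per arm would do. With k = 0.7, power runs from 94.2% (rho 0.3) down to the unadjusted 90.2% (rho 0.7).

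**Step 4. What the switch does.** The rule of a t-test followed by Mann-Whitney was simulated 4,000 times per setting, with 111 per arm, rho 0.5, k = 1 and independent children. A Shapiro-Wilk check at 5% in each arm was assumed as the trigger. The transformation step was not simulated.

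| Follow-up errors | Mann-Whitney used | Type I error of rule | Power of rule | Power, baseline-adjusted |
|---|---|---|---|---|
| Normal | about 10% | 0.051 | 0.90 | 0.96 |
| Skewed (gamma) | about 98% | 0.046 | 0.94 | 0.96 |

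The Monte Carlo standard error at 0.05 is √(0.05 × 0.95 / 4000) = 0.003, so both type I errors are compatible with the nominal level. The shape of the data nevertheless decides almost completely which summary is reported.

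**The case against.** The strongest reply is that {20a} already contains the recommended analysis: a model adjusted for baseline and clustering, presented as assessing the treatment effect on the primary outcome. That stands. What remains is that the model is an addition to the test and is not named as decisive.

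Several stronger readings are tempting, and the documents do not support them.

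- **The test is chosen opportunistically.** The order of the steps is fixed in advance, and analysts see only groups A and B until the analyses are complete (Who will be blinded {17a}; {20c}). Simulated type I error of the switch was near nominal. A diagnostic threshold for the switch may also stand in an analysis plan that is not shown.
- **The trial is underpowered because baseline is left out.** The 111 per arm was calculated for an unadjusted comparison and reproduces. The gain would come on top of the 90% target.
- **The estimated quantity is undefined, or change and 5-month score are two different outcomes.** Instrument, time point, population and model are stated. On the raw scale both forms target the same mean difference under randomization, and with baseline as covariate the treatment coefficient is identical. Only the transformation and the rank test alter the summary.
- **Box-Cox fails because changes can be zero or negative.** The text transforms scores, not changes, and names Box-Cox only as an example.
- **The change score costs at least 18% more families.** That floor needs equal SDs at both visits, which the entry cut makes doubtful.

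The fallback also has some merit: with skewed errors the simulated rule had power of 0.94, against 0.90 for the t-test alone. The adjusted comparison reached 0.96 in the same setting and kept the mean difference, although a larger SD at follow-up would narrow that lead. Rank tests can be extended to clustered and multiply imputed data, but with more difficulty than the planned model.

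**Conclusion.** The point holds as one of precedence, interpretability and efficiency. The leading primary test is unadjusted for baseline, ignores the clustering that the same section expects, and can change scale or summary measure with the data. The model that avoids all three is planned but does not clearly decide the trial.

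The efficiency gain ranges from none to substantial. The variance ratio is 0.65 to 0.85 with equal SDs, and 0.85 to 1.00 with a baseline SD of 0.7 of the follow-up SD, in each case for rho of 0.3 to 0.7. None of these values is in the documents. The direction does not depend on them, because adjustment does not lose precision.

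No alpha inflation from the switch and no shortfall against the stated 90% power is shown. The effect of ignoring clustering in the leading test is not sized here, since the documents give no intra-cluster correlation.

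**What to change.** In {20a}:

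1. Name the multilevel model already planned, for the untransformed 5-month ADHDRS-PI with baseline score as covariate and therapy-group clustering, as the single primary analysis.
2. State that its adjusted mean difference with 95% confidence interval is the primary result and decides superiority.
3. Remove the transformation and the switch to Mann-Whitney from the primary analysis, or keep them, with the Student test, as sensitivity analyses.
4. Address non-normal residuals by a sensitivity analysis of the same mean difference, using robust variance or a bootstrap that resamples therapy groups.

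The cost is a rewording and a little more analysis work. No extra families, visits or measurements are needed, since the baseline score is already collected. Recruitment was still open when the article was written (Trial status) and analysis follows the database freeze ({20c}), so on the article's timetable the change can be fixed before any result is seen.
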